## Abstract

**Introduction:**

The burden of IgE-mediated food allergy in Australian born children is reported to be among the highest globally. This illness shares risk factors and frequently coexists with asthma, one of the most common noncommunicable diseases of childhood. Findings from a case-control study suggest that compared to immunisation with acellular pertussis vaccine, early priming of infants with whole-cell pertussis vaccine may be associated with a lower risk of subsequent IgE-mediated food allergy. If whole-cell vaccination is protective of food allergy and other atopic diseases, especially if protective against childhood asthma, the population-level effects could justify its preferential recommendation. However, the potential beneficial effects of whole-cell pertussis vaccination for the prevention of atopic diseases at a population-scale are yet to be investigated.

**Methods and analysis:**

Analyses of population-based record linkage data will be undertaken to compare the rates of admissions to hospital for asthma in children aged between 5 and 15 years old, who were born in Western Australia (WA) or New South Wales (NSW) between 1997 and 1999 (329,831) when pertussis immunisation in Australia transitioned from whole-cell to acellular only schedules. In the primary analysis we will estimate hazard ratios and 95% confidence intervals for the time-to-first-event (hospital admissions as above) using Cox proportional hazard models in recipients of a first dose of whole-cell versus acellular pertussis-containing vaccine before 112 days old (~4 months of age). Similarly, we will also fit time-to-recurrent events analyses using Andersen-Gill models, and robust variance estimates to account for potential within-child dependence. Hospitalisations for all-cause anaphylaxis, food anaphylaxis, venom, all-cause urticaria and atopic dermatitis will also be examined in children who received at least one dose of pertussis-containing vaccine by the time of the cohort entry, using analogous statistical methods. Presentations to the emergency departments will be assessed separately using the same statistical approach.

## Introduction

Conventional whole-cell pertussis vaccines (wP) were developed between the 1920s and 1940s [1], with subsequent widespread use in combination with diphtheria and tetanus toxoids as a three-dose primary schedule. The reactogenicity of these formulations is thought to be largely driven by the presence of endotoxin, and may manifest as self-limited injection site reactions, fever, irritability and other systemic symptoms [2,3].

The implementation of wP-based primary series in the past century successfully contributed to the near elimination of pertussis in countries like Australia which achieved high immunisation coverage [4]. From 1974, improved access to wP formulations through the Expanded Programme of Immunization has decreased vaccination inequalities in the developing world and the global burden of pertussis disease in children younger than 5 years old [5]. Nevertheless, geographical, social factors and weak health systems still drive vaccine inequity within low and middle income countries, substantially affecting the coverage of the first and third dose of pertussis vaccine primary series, and pertussis-related deaths [5,6]. Development of acellular subunit vaccines (aP) in the 1980s with substantially reduced endotoxin content and improved reactogenicity profile [7], prompted the switchover to aP primary immunisation in most high-income countries over the past 25 years.

In Australia, the transition from wP to exclusive use of aP vaccine formulations for the primary series occurred during the period of 1997 to 1999 [4]. During this period, existing batches of wP were used and fully depleted by community vaccine providers, before being replenished with batches of aP vaccine. This process occurred in a more-or-less stochastic fashion through the jurisdictional immunisation programs. Therefore, the receipt of wP or aP on the day of the first vaccination was not driven by the individual preference of carers or providers, but by which vaccine happened to be available at the primary care services and public immunisation clinics.

The period of switchover from wP to aP in Australia also overlapped with the change from the ninth to the tenth revision of the International Classification of Diseases (ICD) coding scheme. The first edition of ICD-10 AM (AM: Australian Modification) was introduced in New South Wales (NSW) in July 1998, and in Western Australia (WA) in July 1999 [8].

An ecological association has been reported between the transition from wP to aP vaccine in Australia, and an increase in hospital admissions for food-induced anaphylaxis (ICD-9 CM/ICD-10 AM: 995.6/T78) in infants under 12 months old [9]. In the two decades following the replacement of wP, admissions coded as food-associated anaphylaxis increased from 7.3 per 100,000 population in children under 5 years old in 1998/1999 to 30.3 per 100,000 population in 2011/2012 and from 1.7 per 100,000 children 5–14 years old in 2005/2006, to 12.1 per 100,000 children in 2011/2012 [10].

In Australia the prevalence of self-reported “current asthma” in children under 15 years old has declined from 13.5% in 2001 to 9.9% in 2007/2008 [11]. While the rates of all-cause hospitalisation remained stable, paediatric admissions to hospital coded as asthma decreased nationwide by 33% from 1998/1999 to 2010/2011 [12]. Optimisation in the management of acute exacerbations by carers, modifications in admission practices or in the severity of the presentations have been proposed as potential explanations for this trend, yet it remains uncertain the role played by these factors over this period [12]. Admissions to hospital are more likely to occur in those with more severe symptoms, or in those who did not respond well to the initial management in the emergency department. On the other hand, visits to the emergency not only reflect disease severity, but in some circumstances, socio-demographic disparities that negatively impact the access to primary care.

Diagnosis and coding of anaphylaxis in WA improved after 2012, as a result of the implementation of a new guideline for the management of anaphylaxis, and an intensified allergy training program [13]. While this may have improved the ascertainment of cases in this period, it is likely there was also a true rise in the presentations for anaphylaxis in children predominantly driven by tree nut allergy [13].

In the UK, the replacement of the wP-based primary series commenced in September 2004 [14]. Despite a reported increase in hospitalisations for food anaphylaxis between 1998 and 2018 [15]. in a birth cohort of children born from 1998 to 2010, no association was found between the type of pertussis vaccine administered and admissions coded as anaphylactic shock (T78.0) by 12 months old (In text: In an email from [name] ([contact]) in May 2013).

From 2011, the National Institute for Health and Care Excellence in the UK has recommended that children under 16 years old with anaphylaxis should be admitted to hospital [15]. An immediate increase in hospitalisations was observed and hospitalisations for anaphylaxis have continued to increase over the last 5 years [15].

Previous studies have examined the relationship of priming with pertussis-containing vaccines on the development of atopic outcomes in infancy, but had limited power to detect a modest but clinically important difference. A randomised controlled trial of Swedish children born early 1990s found no difference in the cumulative incidence of atopic diseases at 2.5 years old, nor in the frequency of atopic dermatitis or asthma among children vaccinated with wP, aP or diphtheria and tetanus toxoid (DT) vaccines [16]. Similarly, a retrospective cohort study of children born in the Isle of Wight (UK) between September 2001 and August 2002 (a period of shortage of wP) did not show an association either between the type of pertussis-containing vaccine received as a first dose, or the type of pertussis immunization schedule (i.e. wP-only doses versus at least one dose of aP in fully-vaccinated infants for pertussis antigens), and IgE-mediated food allergy, atopic dermatitis and asthma during a 10-year period of follow-up [17]. A retrospective analysis of data from a study of Australian children born between 1997 and 2000 found no association between vaccine type and risk of asthma or atopic dermatitis [18].

Conversely, a case-control study of Australian infants born between 1997 and 1999, the period of changeover to aP-based schedules, reported a lower likelihood of IgE-mediated food allergy in infants primed with a first dose of wP, compared to those that received a first dose of aP [odds ratio: 0.77; 95% confidence interval (CI), 0.62 to 0.95] [19]. The biological plausibility of this finding rests on the differential T-cell polarisation elicited by each type of vaccine. Whereas early priming with aP induces a T helper 2 (Th_2_)-skewed immunophenotype, wP skews T-cell specific memory responses towards Th_1_/Th_17_. This wP-driven immune bias is hypothesised to overcome the physiologic Th_2_ polarisation observed in infants, promoting a more tolerogenic immune environment in those with predisposition to atopy [19].

The above ‘natural experiment’ provided by the programmatic change of pertussis immunisation schedule in Australia, suggests these *in vitro* observations may have clinical consequences. Nonetheless, it remains unproven that a first or subsequent doses of wP in the primary series have a material influence on the subsequent risk of IgE-mediated food allergy, asthma, and or other atopic diseases.

While the current evidence supports the early introduction of peanut and egg into the infants’ diet to prevent peanut and egg allergy, respectively [20], the developmental trajectories of asthma are poorly understood and thus, the development of targeted primary prevention strategies is stalled [21].

Since the implementation of randomised controlled trials in settings where wP has been phased-out would require long-term follow-up of large numbers, observational studies using population-based data represent a potentially valuable source of information. In this paper we describe the methods to compare a birth cohort of children vaccinated with a first dose of wP versus aP with respect to the time to a first or recurrent tertiary care encounter for acute exacerbations of asthma and other atopic diseases.

## Methods

### Study design

The analysis plan described in this protocol is part of a larger project, that aimed to assess Australia’s National Immunisation Program using probabilistic linked data for 1.95 million children born in WA or NSW between 1996 and 2012, encompassing perinatal, birth registries and hospital data, as well as Commonwealth data collections from the Australian Immunisation Register (AIR)—known as Australian Childhood Immunisation Register or ACIR before 2016—and National Death Index. The details of the record linkage procedures have been published elsewhere [22,23].

The cohort for this study will be restricted to all live births in WA or NSW between 1 January 1997 and 31 December 1999. These will be sourced from state birth registries and perinatal data collections (WA Midwives’ Notification System and NSW Perinatal Data Collection) using the above-described linked dataset. The assembled information includes the parent and child’s demographics, maternal obstetric and medical history, labour and delivery details, hospital admissions and presentations to the emergency departments. Hospitalisation data are linked for analysis for the period of January 1997 to December 2013 (WA), and July 2001 to December 2013 (NSW). Presentations to the emergency departments are available from all hospitals in WA from January 2002 to December 2013, and from most public hospitals located in the metropolitan areas of NSW from January 2005 to December 2013 [22].

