### Statistical methods

#### Hospitalisations for asthma

We will compare rates of hospital admissions for asthma in children aged between 5 and 15 years old by means of unadjusted and adjusted Cox regression models for the time-to-first event [31], and Andersen-Gill models for recurrent events using robust standard errors to account for within-child dependence [32].

The person-time-at-risk is depicted in the following Lexis diagrams (Figs 1 and 2).

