**Fig 2 pone.0260388.g002:**
[figure not shown]
Lexis diagram (after data cleaning). Legend: Person-time-at-risk experience of children born in WA or NSW between 1 January 1997 and 31 December 1999 after data cleaning.

Each child will enter the cohort on the date of their fifth birthday and the analysis time will be based on days since entry to the cohort. For time-to-first event analyses, censoring will occur at the earliest of the following: first admission to hospital ICD-coded as ‘asthma,’ the date of death, the day before the 15^th^ birthday, or the end of follow-up (31 December 2013). The same rules will be applied to time-to-recurrent event analyses except there will not be censoring at the time of the first hospitalisation for the outcome of interest. Multivariable models will be stratified by jurisdiction of birth and, where required, non-linear elements (p-splines) will be incorporated.

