#### Emergency department presentations

Emergency department presentations will be analysed using the same statistical approach specified for hospitalisations for asthma, with time zero defined in accordance with the data availability (i.e. the date of the fifth birthday for children born in WA, and the date of the eight birthday for those born in NSW).

All hypothesis tests will be two-sided at 0.05 significance level. All statistical analyses will be carried out in R [33], unless otherwise stated, using the Secured Unified Research Environment from the Sax Institute, NSW.

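### NSW emergency data cover only most metropolitan public hospitals, yet every eligible NSW-born child counts as at risk in the emergency department analysis

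*Protocol article*

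**What the plan says.** All places are in the protocol article.

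- **Coverage.** Study design describes the WA source as complete: "Presentations to the emergency departments are available from all hospitals in WA from January 2002 to December 2013". The NSW source is partial: "from most public hospitals located in the metropolitan areas of NSW from January 2005 to December 2013".
- **Cohort.** Study design sets no residence limit: "The cohort for this study will be restricted to all live births in WA or NSW between 1 January 1997 and 31 December 1999".
- **ED analysis.** The Emergency department presentations paragraph under Statistical methods states: "Emergency department presentations will be analysed using the same statistical approach specified for hospitalisations for asthma". The one adaptation is to time zero: "the date of the fifth birthday for children born in WA, and the date of the eight birthday for those born in NSW".
- **Models borrowed from the asthma section.** Rates are compared "by means of unadjusted and adjusted Cox regression models for the time-to-first event", with Andersen-Gill models for recurrent events. The text after Figure 2 adds: "Multivariable models will be stratified by jurisdiction of birth".
- **Remoteness.** Table 2 marks the remoteness index for inclusion in the models. Bias due to confounding lists it among variables that might differ between wP and aP recipients. It is taken from the mother's address when the child was born.
- **Bias section.** Bias due to missing data covers encounters lost through moves out of the two states. Bias in measurement of the outcome covers ED miscoding. Neither mentions ED visits within NSW that the data source does not cover.

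**The concern.** The plan fits the ED risk set to the limit in time of each state's data, but not to the limit in place given in the same sentence of Study design. An NSW child living outside the covered hospitals' area is counted as at risk from age 8 up to 15, although most of that child's ED visits would go unrecorded.

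Two things follow. Recorded NSW ED rates will be too low. And if, at the same birth date, wP was more or less common in non-metropolitan NSW, one vaccine group holds more of the near-unobservable person-time, and the unadjusted hazard ratio moves without any vaccine effect. The Introduction makes such a pattern possible, since wP stock was run down provider by provider before aP replaced it.

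Remoteness adjustment is the natural protection. It works fully if remoteness has its own effect in each state. If one coefficient serves both states, it has to describe lost recording in NSW and real differences in fully covered WA at once.

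**Working it through.** The protocol gives no ED event count, power or expected hazard ratio, so there is no figure to reproduce. The calculation asks how far a true hazard ratio of 1.00 could be displaced.

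**Inputs from the document:** NSW entry at 8 and WA entry at 5, with exit before 15 (about 7 and 10 years at most; the 31 December 2013 cut-off shortens this for some); stratification by state; a remoteness covariate.

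**Assumed inputs (not in the document):** 75% of children from NSW; 25% non-metropolitan in each state; a share *c* = 0.05 to 0.20 of non-metropolitan NSW visits recorded; wP share 50% in metropolitan areas; true ED rate equal by remoteness in NSW, and 1.3 times higher outside metropolitan areas in WA.

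**Step 1, NSW rate.** Understatement = 0.25 × (1 − *c*): 0.25 × 0.95 = 24% and 0.25 × 0.80 = 20%.

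**Step 2, unadjusted ratio, NSW alone.** With wP share 60% outside metropolitan areas:

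HR = [(0.375 + 0.15*c*) / 0.525] ÷ [(0.375 + 0.10*c*) / 0.475]

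- *c* = 0.05: (0.3825 / 0.525) ÷ (0.3800 / 0.475) = 0.729 ÷ 0.800 = 0.91
- *c* = 0.20: (0.4050 / 0.525) ÷ (0.3950 / 0.475) = 0.771 ÷ 0.832 = 0.93

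With a wP share of 50% everywhere, the ratio is exactly 1.00 at any *c*.

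**Step 3, unadjusted ratio, both states, stratified by state.** WA dilutes the shift. Over a wider set of assumptions (20–30% non-metropolitan, 5–30% recorded), a wP share 10 points higher outside metropolitan areas gives 0.94–0.97 and 10 points lower gives 1.03–1.07. At 20 points the ranges are 0.87–0.94 and 1.07–1.15.

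**Step 4, adjusted ratio, both states, one remoteness coefficient.** Expected counts were fitted with log rate = state baseline + β·wP + γ·remote, the rare-event counterpart of a Cox model stratified by state. True HR 1.00, *c* from 0.05 to 0.20:

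| wP gap, non-metropolitan minus metropolitan | Adjusted HR |
|---|---|
| None | 1.00 |
| 10 points in both states | 1.00 |
| 10 points in NSW, 5 in WA | about 0.99 |
| 10 points in NSW only | 0.97–0.98 |
| +10 points in NSW, −10 in WA | about 0.95 |
| 20 points in NSW only | about 0.95 |

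Reversing the signs in the last two rows gives about 1.05. In the 10-point NSW-only case, adjustment moves the ratio from 0.946 to 0.973 (*c* = 0.05) or from 0.955 to 0.977 (*c* = 0.20), so it removes about half of the shift. With sign-reversed gaps it removes little.

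**Step 5, after the fix.** Adding a state-by-remoteness term, or dropping non-metropolitan NSW children, returns 1.00 in every row. This assumes that residence at birth identifies who is outside the covered area.

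**The case against.** The strongest reply is that the plan already adjusts for remoteness, and that the protocol rests its causal reading on adjusted models. That largely stands. A reader might infer that the NSW ED hazard ratio will depart from 1 with no vaccine effect. The documents do not support this for the adjusted analysis: an NSW-only model with its own remoteness term gives 1.00 under the same assumptions. The 0.91–0.93 in Step 2 is an unadjusted figure, and unadjusted models are open to every confounder.

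A reader might also take it as settled that one remoteness coefficient spans both states. The text does not say so. Stratifying by state can mean separate baselines or separate models, and the state-specific ED entry ages are compatible with separate fits. An article may leave interaction terms to a fuller plan.

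The bias also needs vaccine type to be linked to remoteness given date and state of birth. The protocol says only that this might be so. Elsewhere it calls the stock changeover more or less random and names date and state of birth as the two predictors. Understated NSW rates are not in themselves bias in a hazard ratio. The planned injury negative control might reveal the problem, but the article does not say that it will be run on ED data.

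What remains is that the risk set does not match the stated coverage, the bias section omits this, and the protection depends on a modelling choice left open.

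**Conclusion.** The point holds as a mismatch between risk set and data coverage that is confined to the ED analyses. NSW ED rates will be understated in any case, by 20–24% under the assumed shares. The unadjusted ED hazard ratio is biased only if vaccine type varies with remoteness given date and state of birth; without that link the cost is events and precision.

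For the adjusted ratio, bias from this source is nil if remoteness is fitted by state or if the wP–remoteness pattern is the same in both states. It is small, about 0.97–0.98 for a true 1.00, if the states share one coefficient and a 10-point gap exists in NSW only. It reaches about 0.95 or 1.05 only with gaps of opposite sign or a 20-point gap in NSW alone. All these sizes rest on assumed inputs. A further, unquantified part may remain because residence is fixed at birth, eight years before NSW ED follow-up begins. The primary asthma hospitalisation analysis uses other data and is not affected.

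**What to change.** In the ED analyses:

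1. Restrict the NSW risk set to children whose mother lived in the 'Major cities' category of the remoteness index at the birth, a variable already in Table 2. Keep the all-NSW analysis as a sensitivity analysis.
2. Fit remoteness separately by state, through a state-by-remoteness term or separate state models, and say which.
3. Add the within-NSW coverage gap to Bias due to missing data, and note that NSW ED rates describe the covered area only.

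The cost is one filter, one model term and a few sentences. The few recorded events in regional NSW children leave the main ED analysis. The filter is approximate: residence is measured at birth, only most metropolitan public hospitals report, and the article does not show that 'Major cities' coincides with their catchment.

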### Variables

#### Exposure

We defined the exposure according to the child’s immunisation status.

For the primary analysis, the exposure of interest will be the first dose of pertussis-containing vaccine (wP or aP), irrespective of the type of vaccine given for any subsequent doses.

For the secondary analyses, we will consider the following exposures:

Secondary analysis 1: at least one dose of wP versus aP-only pertussis immunisation, in recipients of a three-dose priming schedule (i.e. excluding children with incomplete schedules).Secondary analysis 2: wP-only versus aP-only pertussis immunisation in recipients of a three-dose priming schedule (i.e. excluding children with incomplete or mixed wP/aP schedules).

During the study period, a single wP formulation was available comprising wP in combination with diphtheria and tetanus toxoid (DTPw, Triple Antigen, CSL, Parkville, Australia), whereas aP vaccines were provided as combination vaccines (Infanrix, SmithKline Beecham and Tripacel, CSL Vaccines, Connaught Laboratories, Canada) comprising DTaP with or without hepatitis B vaccine antigen [24].

The exposure variables will be identified in the AIR dataset, which captures immunisation data from all children enrolled in Medicare, Australia’s universal health insurance scheme [22]. Each dose of the primary course of pertussis vaccines represents a vaccination record. For the purpose of this study, each dose is defined by a single date, dose number, type and brand of pertussis vaccines. Any duplicate immunisation records (i.e. same immunisation date and vaccine dose) have been previously excluded.

Consistent with the aforementioned case-control study [19], children will be excluded from the cohort if a first dose of pertussis-containing vaccine was not recorded, or recorded as given before 39 days or after 111 days of age (~ 4 months old).

